[19]. The relative effect of these agents when used as infusions has not been published and phenylephrine has been used as an infusion in other studies examining rSO_2_. Here, we will use ephedrine (5 mg) in preference to phenylephrine (50-100mcg) as an intravenous bolus medication for the treatment of intraoperative hypotension when heart rate is less than 80 beats per minute. Phenylephrine by infusion (200mcg/ml) will be titrated to maintain blood pressure within 20% of preoperative mean arterial pressure (MAP) when there has been a requirement for more than 400mcg of phenylephrine over a 20 min period. Pre-treatment with ephedrine significantly blunts the decrease in rSO_2_ seen with bolus phenylephrine for at least 20 min
[19]. If phenylephrine bolus dose is used as the first treatment for intraoperative hypotension we will delay the recording of results following a trial intervention by at least 8 min.

For MAPs greater than 70-80 mmHg associated with intraoperative bleeding the initial treatment will be to ensure adequate depth of anesthesia (BIS 40–60), followed by administration of incremental boluses of fentanyl 25mcg, up to a maximum dose of 2.5 mcg/kg. Failure of this to achieve the required reduction in blood pressure will result in the administration of the antihypertensive medications labetolol or hydralazine at the discretion of the patient’s anesthesiologist.

Standard American Society of Anesthesiologists monitoring will be used for all patients. The BIS Quatro electrode will be placed diagonally on the patient’s left forehead. Cerebral oxygenation will be measured using the INVOS 5100C monitor (Covidien, Boulder, CO). Optodes will be applied, before induction of anesthesia, by a single trained researcher on either side of the BIS Quatro sensor as recommended by the manufacturer.

Following induction of anesthesia, FIO_2_ and minute ventilation will be sequentially adjusted to achieve:

1) FIO_2_ 30% (70% nitrogen), PETCO_2_ 30 mmHg – supine position.

2) FIO_2_ 30% (70% nitrogen), PETCO_2_30mmHg – beach chair position.

3) FIO_2_ 100%, PETCO_2_ 30 mmHg – beach chair position.

4) FIO_2_ 100%, PETCO_2_ 45 mmHg – beach chair position.

5) FIO_2_ 30%, PETCO_2_ 30 mmHg – beach chair position.

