### Statistical considerations

#### Power

The reported mean rSO_2_ is 67.1% ± 6.2 for patients placed in beach chair position
[7]. Based on a previous investigation
[11], we expect a 6–8 percentage point difference in rSO_2_ resultant upon the planned change in FIO_2_ and a 2–4 percentage point difference resultant upon the planned change in PETCO_2_. A total percentage point increase in excess of 10 would be of clinical significance. A sample size of 48 will have a power of greater than 0.8 to detect a 4-5% in the planned pairwise comparisons. Allowing for an approximately 10% drop out 54 subjects will be recruited, targeting 24 patients in each group randomized to an anesthetic. The power for the comparison between the two anesthetic regimens is better than 85% for a difference of 6% which would be a clinically important difference for the secondary outcome.

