#### Analysis

Data will be analyzed with a repeated measures two-way analysis of variance in which ventilation strategy is the within-subjects factor and anesthetic regimen is the between-subjects factor. Residuals will be assessed for normality and equal variances; if necessary, the analyses will be adjusted. The primary analysis will focus on the comparison between the ventilation strategies. A post hoc Tukey’s HSD procedure will be used to correct for all pairwise comparisons between ventilation strategies.

The effect of desflurane or propofol on cerebral desaturation and a possible differential response to changes in ventilation strategy will be evaluated as a secondary outcome measure. Analysis for the primary outcome will be adjusted if interaction effects between ventilation strategy and the anesthetic used are significant. A p value of <0.05 will be considered statistically significant.

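### The levels of the ventilation factor are not fixed; if the supine set point is one of them, an anesthetic difference in the fall on positioning can register as a differential response to ventilation.

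*Protocol article*

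**What the plan says.** **Set points (protocol article, Methods/design).** After induction, FIO2 and "minute ventilation will be sequentially adjusted to achieve" five numbered conditions. The first is FIO2 30% with "PETCO_2_ 30 mmHg – supine position". The second has the same FIO2 and the same PETCO2 target, "30mmHg – beach chair position". The third raises FIO2 to 100%, the fourth also raises PETCO2 ("45 mmHg – beach chair position"), and the fifth returns to the settings of the second. Only the first is supine.

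**Model (Statistical considerations, Analysis).** There is one repeated measures two-way analysis of variance, in which "ventilation strategy is the within-subjects factor and anesthetic regimen is the between-subjects factor". Position is not a factor, the levels of the ventilation factor are not listed, and the supine reading is neither included nor excluded.

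**Secondary outcome (same section).** It has two parts: the anesthetic effect on cerebral desaturation, and "a possible differential response to changes in ventilation strategy will be evaluated as a secondary outcome measure". No separate contrast is given for either part. A significant interaction between ventilation strategy and anesthetic leads to adjustment of the primary analysis.

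**Aims (end of Background; start of Methods/design).** The FIO2 and PETCO2 question is limited to patients in the beach chair position.

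**The concern.** The step from set point 1 to set point 2 changes posture and leaves both ventilation targets alone. If set point 1 is a level of the factor called ventilation strategy, the interaction with anesthetic is a 4-df test that mixes two questions: whether the agents differ in how far rSO2 falls on sitting the patient up, and whether they differ in the response to oxygen and carbon dioxide. These correspond to the two parts of the secondary outcome.

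Suppose one agent preserves rSO2 better on positioning by d points, and both arms then respond identically to the gas changes. The arm differences over the five set points are (0, d, d, d, d). They are not constant, so this is an interaction by definition.

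Two things are at stake. A significant result could be reported as an agent-specific response to FIO2 or PETCO2 when it arose from posture. It could also trigger the adjustment rule for a primary analysis whose question concerns the beach chair position only. The scenario is plausible on the protocol's own account: the Discussion cites better preserved cerebral oxygenation with an inhalational regimen than with a propofol regimen in the beach chair position, while noting possible confounding in that comparison.

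**Working it through.** **Inputs from the protocol.** SD 6.2 (Power), 24 per arm (Power), significance at p < 0.05 (Analysis; taken as two-sided for the t test).

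**Inputs assumed.** Compound symmetry, no arm difference when supine, and within-patient correlation ρ of 0.3, 0.5 or 0.7. The document gives no correlation.

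**Step 1: reproduce the plan's own figure.** The Power section gives power for the anesthetic comparison as "better than 85% for a difference of 6% which would be a clinically important difference for the secondary outcome". For a two-sample t test, the noncentrality is 6 / (6.2 × √(2/24)) = 3.35 on 46 df, and power is 0.907. The stated bound holds. It reproduces as a difference in level between arms; the protocol does not present it as a difference in the fall on positioning.

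**Step 2: noncentrality of the interaction.** For k set points and arm-difference vector v,

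λ = (n/2) × Σ(v_j − v̄)² / [SD² × (1 − ρ)], with df k − 1 and (k − 1)(2n − 2).

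For v = (0, d, d, d, d), Σ(v_j − v̄)² = d² × (1 − 1/5) = 0.8d². With n = 24 and SD² = 38.44,

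λ = 12 × 0.8d² / [38.44 × (1 − ρ)] = 9.6d² / [38.44 × (1 − ρ)], on 4 and 184 df.

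Example: for d = 6 and ρ = 0.5, λ = 345.6 / 19.22 = 17.98.

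**Step 3: probability of a significant five-level interaction, with identical gas responses in both arms (noncentral F).**

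| Positional difference d | ρ = 0.3 | ρ = 0.5 | ρ = 0.7 |
|---|---|---|---|
| 2 points | 13% | 17% | 26% |
| 3 points | 25% | 35% | 56% |
| 4 points | 44% | 59% | 84% |
| 6 points | 82% | 94% | 99.6% |

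**Step 4: the same on set points 2–5.** The vector is (d, d, d, d), so Σ(v_j − v̄)² = 0, λ = 0 and the rejection rate is 5% for every d. A simulation of 4,000 trials at ρ = 0.5 agrees: five levels give 60% for d = 4 and 93% for d = 6; four levels give 5.1% for each.

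**Step 5: what dropping the supine point costs.** Take a true 3-point arm difference in gas response, with no positional difference.

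- FIO2 response: (0, 0, 3, 3, 0) has Σ = 18 − 36/5 = 10.8; on set points 2–5, Σ = 18 − 36/4 = 9. Power, five against four levels: 37% v 35% (ρ = 0.3), 51% v 48% (ρ = 0.5), 76% v 72% (ρ = 0.7).
- PETCO2 response: (0, 0, 0, 3, 0) has Σ = 9 − 9/5 = 7.2; on set points 2–5, Σ = 9 − 9/4 = 6.75. Power: 25% v 27%, 35% v 37%, 56% v 58%. The loss in Σ is more than offset by testing 3 df rather than 4.

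**The case against.** The strongest reply is that the protocol never says the supine reading is a level of the factor. Set points 1 and 2 have the same gas targets, so read literally they are one ventilation strategy in two postures, and the aims are confined to the beach chair position. Treating the supine reading as a reference fits the text too. Factor levels may also be left to an analysis plan that is not shown. This stands as a reason to word the point conditionally. It does not dispose of it, because the protocol itself fixes the model, the single within-subjects factor and the interaction rule, and the five set points are the only list of levels it offers.

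Four stronger conclusions might be inferred, and the documents do not support them:

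- *A positional effect will be declared a ventilation effect.* The percentages are probabilities of a significant omnibus test. A wrong conclusion also requires that nobody looks at where the interaction arises, and set-point means by arm would show it.
- *The two parts of the secondary outcome cannot be told apart.* All the readings needed to separate them are collected, and Methods/design defines sustained desaturation events and has them recorded separately.
- *The agents must be alike when supine.* This is an assumption. The Discussion cites rSO2 rising with desflurane depth in supine patients. An arm difference already present at set point 1 and constant thereafter is a main effect and produces no interaction.
- *The primary estimate is biased.* Under the pattern examined, the differences between set points 3 and 2 and between 4 and 3 are the same in both arms, so the pooled contrasts are unaffected. What is shown is a needless trigger of a rule whose form is not specified.

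**Conclusion.** The point holds conditionally. The levels of ventilation strategy are not fixed. On the five-level reading that the list of set points suggests, the interaction with anesthetic includes a step that changes posture alone. A purely positional anesthetic difference can then give a significant interaction and set off adjustment of the primary analysis, with no difference in response to oxygen or carbon dioxide.

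The size depends on the positional difference and on a correlation the protocol does not state. Over ρ = 0.3–0.7 the probability runs from 25–56% at 3 points to 82–99.6% at 6, against the nominal 5% when only the beach chair set points are used. If the supine reading was always meant as a reference, the problem disappears, but the text has to say so. This is a worthwhile, low-cost clarification of a secondary analysis and of the rule tied to it.

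**What to change.** In the Analysis section:

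1. State that the ventilation-by-anesthetic interaction is tested on set points 2–5 only, and report two component contrasts: anesthetic × (set point 3 − set point 2) for FIO2, and anesthetic × (set point 4 − set point 3) for PETCO2.
2. Test anesthetic × (set point 2 − set point 1) as a separate contrast, labelled as the anesthetic effect on the fall with positioning.
3. State that only the beach chair interaction counts as a differential response to ventilation and can trigger adjustment of the primary analysis.

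This takes a few sentences and no new data. For a 3-point difference, the cost is about 2–4 percentage points of power for the FIO2 response and none for the PETCO2 response.

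### A significance test for interaction on the same data may change the primary analysis, and neither the 5% error rate nor the N=48 power is secured once it does

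*Protocol article*

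**What the plan says.** The Analysis section specifies a two-way repeated measures analysis of variance in which "ventilation strategy is the within-subjects factor and anesthetic regimen is the between-subjects factor". The primary focus is the comparison between ventilation strategies, and multiplicity is handled as follows: "A post hoc Tukey’s HSD procedure will be used to correct for all pairwise comparisons between ventilation strategies". The interaction has secondary status: "a possible differential response to changes in ventilation strategy will be evaluated as a secondary outcome measure". The next sentence nevertheless lets it act on the primary analysis: "Analysis for the primary outcome will be adjusted if interaction effects between ventilation strategy and the anesthetic used are significant". The only significance threshold in the section is "A p value of <0.05 will be considered statistically significant".

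The Power section supports the primary comparisons with "A sample size of 48 will have a power of greater than 0.8 to detect a 4-5% in the planned pairwise comparisons". It gives a separate figure for the comparison between anesthetics at 24 per arm. It gives no power for ventilation comparisons within one anesthetic.

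**The concern.** How the primary question is analyzed depends on a preliminary test in the trial's own data. The familiar response to a significant interaction is to compare set points separately within each anesthetic. Two things then change.

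- When there is truly no effect, the arms are examined separately exactly in those trials where chance has pushed their profiles apart. Tukey's procedure controls error within one set of pairwise comparisons. It does not cover the selection step or the second set of comparisons.
- Each comparison rests on 24 patients, while the stated power is for 48.

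The adjusted branch is a realistic prospect. Methods/design says the two agents were chosen because they differ in their effects on cerebral vasodilation, autoregulation and CO2 responsiveness. An interaction is therefore plausible, particularly at the PETCO2 step, which has the smallest expected effect (2 to 4 points).

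**Working it through.** **Inputs from the article.** SD 6.2 points ("The reported mean rSO_2_ is 67.1% ± 6.2 for patients placed in beach chair position"); 48 patients, 24 per arm; five set points, four of them in the beach chair position; significance level 0.05.

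**Assumptions.** Two-sided testing, sphericity, and a within-patient correlation ρ, which the article does not give and which is therefore varied. The adjustment is taken to be Tukey comparisons within each arm, with a significant difference in either arm counting as a finding.

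**Step 1: reproduce the stated power.** For a pairwise comparison of k set points in n patients, the standard error of the difference is 6.2 × √(2(1−ρ)/n). The critical value is q(0.95; k, df)/√2, and power comes from the noncentral t distribution.

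- With k=5, n=48 and ρ=0, the standard error is 6.2 × √(2/48) = 1.266 and the critical value is 3.896/√2 = 2.755 (df 46 × 4 = 184).
- Power is 66% at 4 points, 79% at 4.5 and 88% at 5. With k=4 it is 71%, 83% and 91%.
- The difference detectable with 80% power is 4.56 points (k=5) or 4.36 (k=4).

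The stated figure, above 0.8 for 4 to 5 points, therefore reproduces even at zero correlation, apart from the lower end of the range. At k=5, 4 points reaches 80% once ρ is about 0.23.

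**Step 2: the same comparison within one arm.** With k=5, n=24 and ρ=0, the standard error is 6.2 × √(2/24) = 1.790 and the critical value is 3.935/√2 = 2.783 (df 23 × 4 = 92).

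| ρ (assumed) | n=48: 4 points | n=48: 5 points | n=24: 4 points | n=24: 5 points |
|---|---|---|---|---|
| 0 | 66% | 88% | 30% | 51% |
| 0.5 | 96% | 99.8% | 65% | 88% |
| 0.7 | 99.9% | >99.9% | 90% | 99% |

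At ρ=0 the difference detectable with 80% power rises from 4.56 to 6.50 points. Within an arm, 80% power needs ρ of about 0.62 for 4 points and 0.41 for 5. The expected 6 to 8 point FIO2 effect has 71-95% power within an arm at ρ=0, and at least 97% at ρ=0.5.

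**Step 3: error rate of the two-path rule.** The simulation used 1,000,000 trials for each k, 24 per arm, with no ventilation effect and no interaction. Pooled Tukey was applied when the interaction p was 0.05 or more, and Tukey within each arm otherwise.

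- The interaction is falsely significant in 5.0% of trials.
- In those trials, at least one within-arm comparison is falsely significant in about 55% (k=5) to 57% (k=4). The pooled analysis would err in about 6% of the same trials.
- In the other 95% of trials the pooled analysis errs in about 5.0%.

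For k=5 this combines to 0.95 × 5.0% + 0.05 × 54.6% = 4.75% + 2.73% ≈ 7.5%. Over k=4 and k=5 the simulated rate is 7.4-7.6%, against 5.0% for pooled Tukey alone. Testing each arm at 0.025 in the adjusted branch lowers it only to about 6.5-6.6%.

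**The case against.** The strongest reply is that the article says the analysis will be adjusted. It does not say that it will be split by arm. If the adjustment keeps the interaction term and reports marginal means, a balanced design has no inflation and no loss of power. If a ventilation effect is claimed only when both arms show a significant difference, the simulated error rate is about 4.8-5.0%, again without inflation. What the adjustment consists of may also be set out in a full protocol or analysis plan that is not shown.

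This stands, and it limits the point. The missing definition is not by itself the complaint. The conditional trigger is stated in the article, and a definition elsewhere would leave it in place. The harmless reading also gives the sentence little to do, because testing the interaction already requires fitting that term in the two-way model.

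The size is also fairly contested. The excess is about 2.5 percentage points. It arises in a branch entered in 5% of null trials and is computed under no ventilation effect at all, whereas the article expects effects. The roughly 55% false-positive rate among triggered trials is the same excess seen conditionally, not a further problem. Following a significant interaction with within-arm comparisons is conventional practice.

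A reader might infer that a non-significant interaction makes pooling unsafe, since the test is weak at 24 per arm. That does not follow: an equally weighted contrast over two randomized arms is valid whether or not there is an interaction.

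**Conclusion.** The point holds in a limited form. The article lets an interaction test at p<0.05 alter the primary analysis and states no error control over the two paths. Under the usual within-arm adjustment, with either arm counting, family-wise error is about 7.5% instead of 5.0%. Power for 4 to 5 points then ranges from 30-51% to 90-99%, depending on a correlation the article does not give.

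A reader might go further and infer that the plan certainly switches to separate analyses, inflates its error rate and misstates its power. The documents do not support that. The form of the adjustment is not stated, and at least two readings cause no inflation. The power above 0.8 is claimed only for 48 patients, where it reproduces, so no stated figure is wrong. This is a cheap improvement, not a flaw that undermines the trial.

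**What to change.** Replace the conditional sentence with a fixed rule. The primary analysis is the set of Tukey-adjusted set-point contrasts from the two-way model, averaged equally over the two anesthetics, whatever the interaction test shows. As secondary results, always report the contrasts within each anesthetic and their between-arm differences, with 95% confidence intervals. This matches the article's own ranking of the differential response as secondary, holds the family-wise error at 5.0% under the assumptions above, and keeps the N=48 basis of the power statement.

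The cost is wording only, with no change to sample size or data collection. The drawback is that with a large interaction the averaged contrast describes neither arm well, so the arm-specific estimates must be shown and interpreted beside it.

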## Discussion

Ensuring the safety of patients anesthetized in the beach chair position is of widespread and significant interest. The simple modulation of inspired gas composition has proven to reliably improve cerebral oxygenation measured by NIRS in normal awake subjects
[10], healthy supine anesthetized patients
[11] and patients undergoing carotid endarterectomy with either regional or general anesthesia
[4,5]. The major aim of the proposed study is to determine the best ventilation strategy to maintain cerebral oxygenation and limit neurological risk in patients anesthetized in the beach chair position. We will investigate the response, the magnitude of the response and the direction of the response in rSO_2_ resultant upon changes in FIO_2_ and PETCO_2_.

Controversy exists regarding the effect of beach chair position and anesthesia on cerebral oxygenation and its measurement. Although it has been suggested that cerebral oxygenation should be monitored in all patients anesthetized in the beach chair position
[20] this is certainly not yet a standard of care. While severe cerebral desaturation has been effectively measured using the INVOS series of cerebral oximeters
[12] similar findings are not evident when NIRO instruments are used
[21] despite the fact that both technologies are based on NIRS. Invasive jugular venous bulb saturation (Sjv0_2_) may be a more sensitive technique for the detection of cerebral desaturation
[22], but unless routine shoulder surgery is relocated from specific ambulatory surgery centers where invasive techniques are neither available nor encouraged, one must first consider a non-invasive solution.

In terms of anesthetic choice, the balance between cerebral blood supply and oxygen demand is our main concern. Propofol proportionally decreases cerebral blood flow (CBF) and cerebral metabolic rate for oxygen (CMRO_2_) without affecting cerebral ateriovenous oxygen difference
[23]. Desflurane causes a reduction in CMRO_2_ but the expected reduction in cerebral blood flow is overcome by direct cerebral vasodilation. The decrease in CMRO_2_ and cerebral vasodilation are greater with desflurane when compared to other inhalational agents
[15]. Regional oximetry values increase in supine patients with increasing anesthetic depth of desflurane
[24] and cerebral desaturation is more frequently observed during one lung ventilation while using TIVA with propofol compared to inhalational anesthesia
[14]. Cerebral oxygenation is reported to be better preserved with sevoflurane-nitrous oxide anesthesia when compared to propofol-remifentanil anesthesia for patients placed in beach chair position
[22], but nitrous oxide and remifentanil may have acted as uncontrolled confounding factors. Here we will compare desflurane to TIVA with propofol and control all other aspects of anesthesia. In conclusion, the proposed study is the first to investigate specifically the effects of ventilation strategies and specific anesthetic agents on cerebral oxygenation in patients anesthetized in the beach chair position.

